#### Secondary outcomes

(i)Psychometric properties of the HLS-EU-Q12 [36] questionnaire which is a 12-item questionnaire and was developed and evaluated in European countries for measuring health literacy. There are no validated tools for measuring health literacy in Bangladesh where HLS-EU-Q12 could potentially be used. However, it is unknown whether all items are appropriate as in Bangladesh. Therefore, assessing the reliability and validity of the HLS-EU-Q12 tool is a secondary outcome. Psychometric properties of the HLS-EU-Q12 [36] will be assessed at baseline only.(ii)Level of health literacy at baseline. After assessing the psychometric properties, we may come up with all 12 items or remove one or two items. Based on the validated tool, we will estimate the health literacy among the participants with high blood pressure. The outcome measure will be the proportion of people who have different levels of health literacy such as above or below average. The level of health literacy will be estimated at baseline only.(iii)The proportion of the smoker who smoked at baseline and at 6 months, and the proportion of smokers who intend to quit or reduce smoking within 1 month or 3 months at baseline and achievement after the intervention. Time frame: (1) baseline and (2) immediately after the intervention (6 months).(iv)The proportion of people who take regular physical exercise and who intend to take part in physical activities. To measure this outcome, the GPAQ [42] tool will be used. The difference in the proportion of participants who take part in regular exercise was measured at baseline and at follow-up. Time frame: (1) baseline and (2) immediately after the intervention (6 months).(v)The proportion of people who use their own mobile phone, can read SMS, and have the intention to receive and pay for SMS for health information. Time frame: baseline only.(vi)Perception of and practice in raw salt consumption. The outcome measure is the proportion. Tool: a modified version of Q-MAT [43]. Time frame: (1) baseline and (2) immediately after the intervention (6 months).(vii)Perceived barriers and enablers in participating and adopting lifestyle modifications to manage blood pressure. This is descriptive information. The software NVivo will be used to investigate if there are any common themes of barriers which could intervene. Time frame: immediately after the intervention (6 months).

### Participant timeline and outcome measures

All participants are recruited from December 2020 to March 2021. Intervention, outcome measures, and timeline are shown in Table 1.

**Table 1 Tab1:** Time schedule of enrolment, interventions, and outcome measures

	Recruitment and baseline data collection	Intervention and follow-up assessment
Time schedule	December 2020–March 2021	May 2021–November 2021
Parameter assessments		
(i) Blood pressure	√	√
(ii) Participant information including age, gender, level of education, occupation, and self-reported medical history	√	
(iii) Health literacy data using the shorter version of the European Health Literacy Survey Questionnaire HLS-EU-Q12 [36]	√	
(iv) Smoking cessation motivation questionnaire (Q-MAT) [43]	√	√
(v) Global Physical Activity Questionnaire (GPAQ) [44, 45]	√	√
(vi) Dietary motivation questionnaire, which is a modified version of the smoking cessation motivation questionnaire (Q-MAT)	√	√
(vii) Information related to the use of a mobile phone in managing blood pressure	√	
(viii) Qualitative data on perceived barriers and enablers in changing lifestyle in managing blood pressure	√	√
(ix) Information on willingness to adopt the lifestyle change activities		√
(x) Information on willingness to continue the activities after the intervention		√
(x) Information on the effectiveness of the intervention components		√

Data analysis and manuscript writing from the baseline data from March 2021 to October 2021 (until follow-up assessments)

### Participants and collection of qualitative information

A nested qualitative study will be conducted within the trial design. Semi-structured in-depth interviews will be used to capture the perspectives and experiences of the project and perceived barriers and enablers faced to change lifestyle activities in managing blood pressure. Data will be collected at the beginning of the study and at the end of the program.

#### Participants

We will select 25 participants: 20 from the intervention arm and five people involved in the research or are aware of local health systems and aware of barriers and opportunities to manage health and well-being in the community. Firstly, we will randomly select four villages from the nine villages of the intervention group. Secondly, we will select five participants: at least two women, one farmer, one employee, and one business person. The proposed choice will represent gender and occupation. This is expected that the proposed selection will also represent the education level. Although the sample is not entirely random, overall, it will represent the intervention group. Other than the study participants, the five people will include one physician who will help deliver blended lectures, the study coordinator, one retired bank officer, the principal of the ORCD college, and a community leader. Previous studies have demonstrated that in this setting 25 participants would be acceptable [46, 47].

#### Qualitative data collection

Two investigators will conduct semi-structured interviews—the chief investigator from Australia through Zoom and another investigator from the ORCD at the study location. A set of open-ended questions will guide the interviews. Through the interview, topics will be covered on the current barriers of the intervention program. The format will allow for additional questions and issues to be covered as they arise throughout the interview. The responses by the participants will be recorded, but their identification will not be disclosed. The questions will include:

Q1: Could you please tell me how easy or difficult it is to access health services to manage chronic diseases, including hypertension?

Q2: What do you recommend for overcoming the problems of access to appropriate health services in your locality?

Q3: To attend regular exercise programs, what are the barriers to participation?

Q4: What would you recommend for overcoming the barriers to lead a healthy life?

Q5: Currently, more than 40% of adults smoke. What do you consider the barriers to quitting smoking?

Q6. What would you recommend for quitting smoking?

### Statistical analyses

Although the intervention will be conducted as clusters, data will be collected as individuals within clusters and the effect of the intervention will be measured based on individual’s data. Since the randomization is based on clusters, there might occur differences in baseline characteristics of participants. The baseline characteristics for the intervention and the control group will be examined using the chi-square test or Fisher’s exact test for categorical variables and the two-sample *t-*test or Mann-Whitney U test for continuous variables depending on the distributions of the data.

The effect size will be the mean difference in the primary outcome. The comparison will be made between differences for control and intervention groups after the follow-up. More specifically, it could be shown as the difference between DifCon and DifInt. DifCon equals the difference between baseline and follow-up for the control group, and DifInt equals the difference between baseline and follow-up for the intervention group. Such comparison will give the actual effect size due to the intervention. Generalized linear model (GLM) will be used for analytical purpose, and the models will be adjusted for factors which are different between control and intervention groups at baseline. For the secondary outcomes (motivation to smoking cessation, change in dietary patterns, and physical activity), chi-square tests will be used to detect any associations in the outcome variables across gender, age categories, level of education, and socioeconomic status. The difference in proportion with 95% confidence interval between control and intervention groups will be computed using the test of proportion, and odds ratios (OR) with 95% confidence interval will be computed using logistic regression techniques. The models will be adjusted for covariates as appropriate.

Rasch analysis using RUMM30 software will be used to investigate the psychometric properties of the Health Literacy tool and to compute the overall score from the 12-item HLS-Q12 tool. Individual item, as well as the overall score from all items combined, will be compared for gender, age group, level of education, occupation, and SES using chi-square, *t*-tests, or ANOVA as it is appropriate.

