## Methods

Study design: a single-center, cluster randomized control trial (RCT). Control:intervention = 50%:50%

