### Cluster randomization

Randomization will be performed after the recruitment of all participants and the baseline data collection. The entire 18 villages will be divided into two clusters: one cluster is with nine villages, about 50% of the study location, and the other cluster is with the remaining nine villages. The clusters are the unit of randomization. Each cluster has 150 participants; 10 to 20 participants are from each village based on the village size within a cluster. The intervention and the control group will not be divided into mutually exclusive groups based on risk factors for high blood pressure. This is because (i) this is highly likely that both clusters will have similar risk factors for high blood pressure and (ii) the intervention will be more practical given the nature of the intervention where participants will work as a team formed in different villages.

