### Sequence generation

Statistically, a simple random sampling technique (an unbiased coin toss) will be used to select the intervention group. The cluster is the unit of randomness but not the individual participants within clusters. However, within a cluster, we will aim to recruit participants with a male to female ratio equivalent. In that case, the restriction is to recruit one male after recruiting one female participant to make the sex ratio equivalent. Therefore, no random sequence will be generated. However, the complete list of potential percipients with hypertension is available from the previous cross-sectional study [15]. The study location, participants, and their socioeconomic condition can be accessed from the Narail district statistics [40].

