### Implementation of the intervention

#### Intervention

In the intervention arm of 150 participants, the ORCD investigators will form at least ten teams, led by a volunteer leader who will lead the teams and communicate with the project investigator or the doctor if it is necessary. The intervention arm will involve (i) delivering a blended learning education program, including delivering printed materials, and (ii) weekly phone calls to the team leaders. The intervention is an educational program focused on awareness of a healthy lifestyle, including motivation to participate in regular physical activity, community engagement, and keeping frequent contact with health professionals. The chief investigator will keep a record of each team and communicate with the team leaders once every week to remind them to adhere to the intervention program. The weekly monitoring program will continue until the study ends.

The lectures will be delivered to ten teams, comprised of about 15 participants in each team, and will be led by a volunteer team leader using the ORCD’s laptop, overhead projector, and sound system in local clubs, school premises, or participants’ houses. The ORCD investigator, including the physician and an information technology person, will assist with the education programs. Where required, the physician will add interpretations or additional explanations following WHO guidelines and recommendations [41].

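### The stated analyses assume independent participants in a cluster-randomised trial, so error bars for blood pressure and the between-arm smoking, exercise and salt outcomes are too small

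*Protocol article*

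**What the plan says.** The protocol article calls the design cluster randomised, with equal arms. Under Cluster randomization it says "The entire 18 villages will be divided into two clusters: one cluster is with nine villages", the remaining nine villages form the other, and "The clusters are the unit of randomization". Each cluster holds 150 participants, 10 to 20 per village. Under Sequence generation, a coin toss decides which cluster receives the intervention.

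Under Statistical analyses, the clustering is acknowledged but "the effect of the intervention will be measured based on individual’s data". For blood pressure, "Generalized linear model (GLM) will be used for analytical purpose", with adjustment for whatever differs between the arms at baseline. For smoking, diet and physical activity, a test of proportion is named and "odds ratios (OR) with 95% confidence interval will be computed using logistic regression techniques", with covariates as appropriate. The Abstract names analysis of covariance. No random effect, GEE, cluster-robust variance, cluster-level summary or ICC is mentioned. The only consequence drawn from cluster randomisation is that baseline characteristics may differ.

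Delivery adds further grouping: "In the intervention arm of 150 participants, the ORCD investigators will form at least ten teams", each of about 15 people sharing a volunteer leader and group lectures.

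**The concern.** People in one village share diet, environment, health services and possibly the same measurement team on the same day. In the intervention arm they also share a team leader and sessions. Their outcomes, and their changes over six months, are likely to be correlated. The named methods, in their ordinary form, count each participant as a separate piece of evidence. Adjusting for baseline covariates can remove some imbalance, but it does not restore a standard error computed as if participants were independent.

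At stake is the error rate of the primary SBP and DBP comparison and of the between-arm smoking, exercise and salt comparisons. A programme with no effect could be declared effective more often than the nominal level allows, and the Discussion intends the results to inform wider prevention programmes.

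**Working it through.** **Inputs.** From Cluster randomization: two clusters, 18 villages, 150 participants per arm. From Sample size: 106 evaluable per arm, difference 5 mmHg, SD 12 mmHg, significance level 0.01, power 95%. Assumed, because the protocol gives none: an ICC of 0.01 to 0.05, used for villages and for the two areas alike.

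**The plan's own figure.** For two independent means, n per group = 2 × [12 × (2.576 + 1.645)/5]² = 205.2, so 206. The stated 106 does not reproduce; with 106 per group, two-sided power at 0.01 is 67.6%. That is a separate point. It matters here for two reasons: the stated calculation has no clustering allowance, and 106 is the evaluable number used below.

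**Formulas.** Design effect DE = 1 + (m − 1) × ICC, where m is participants per unit. The naive standard error is too small by the factor √DE. Actual size of a nominal level-α test = 2 × [1 − Φ(z(1−α/2)/√DE)].

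**Units.** Village: m = 106/9 = 11.8 or 150/9 = 16.7. Randomised cluster: m = 106.

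| Unit counted | m | ICC | DE | √DE | Size at nominal 5% | Size at nominal 1% |
|---|---|---|---|---|---|---|
| Village | 11.8 | 0.01 | 1.11 | 1.05 | 6.3% | 1.4% |
| Village | 11.8 | 0.05 | 1.54 | 1.24 | 11.4% | 3.8% |
| Village | 16.7 | 0.01 | 1.16 | 1.08 | 6.8% | 1.7% |
| Village | 16.7 | 0.05 | 1.78 | 1.34 | 14.2% | 5.4% |
| Two clusters as written | 106 | 0.01 | 2.05 | 1.43 | 17.1% | 7.2% |
| Two clusters as written | 106 | 0.05 | 6.25 | 2.50 | 43.3% | 30.3% |

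Last row worked out: 1 + 105 × 0.05 = 6.25 and √6.25 = 2.50. Then 1.960/2.50 = 0.784, which gives 43.3%, and 2.576/2.50 = 1.030, which gives 30.3%.

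A simulation of the two-cluster case (10,000 trials, 106 per arm, ordinary t-test) gave 17.5% and 43.6% at nominal 5%, and 7.3% and 30.5% at nominal 1%, for ICC 0.01 and 0.05.

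**What a village-level analysis can and cannot repair.** With 18 randomised villages there are 18 − 2 = 16 between-unit degrees of freedom. With two randomised clusters there are 2 − 2 = 0, so the variance between the randomised units cannot be estimated from the data.

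As an illustration, assume village variance is 0.02 of the total and area variance 0.01, with 11.8 people per village:

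- Variance of a village mean within an area: 0.02 + 0.97/11.8 = 0.102 of the total.
- Variance of the arm difference that the 16-df test can see: 2 × 0.102/9 = 0.0227.
- Area variance that it cannot see: 2 × 0.01 = 0.02.
- The standard error is too small by √(0.0427/0.0227) = 1.37.
- The critical value 2.120 becomes 2.120/1.37 = 1.55. On t with 16 df that is an actual size of about 14% at nominal 5%.

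With area variance 0.02, the same steps give a factor of 1.67 and a size of about 22%.

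**The case against.** **Individual data do not imply independence.** Mixed models and GEE also use individual records, and GLM names a family of models, not a variance estimator. That is right about the quoted sentence taken alone. But the section goes on to name a test of proportion and logistic regression, the Abstract names ANCOVA, and the only adjustment listed is for covariates.

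**The detail may be in an analysis plan that is not shown.** Silence alone would be no finding. Here the protocol names its tests and its adjustment set, so it has fixed a method. The sample-size calculation ignores clustering too, which points the same way.

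**The size of the inflation is unknown.** This stands. The ICC is assumed. The primary contrast is a difference in change, which removes stable village differences, so the relevant ICC is that of change and may differ from that of raw blood pressure. The direction holds for any positive value.

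**Two stronger readings are not supported.** A reader might infer that every secondary outcome is affected. The Secondary outcomes section does not bear this out: the health-literacy and mobile-phone outcomes are baseline only and the barriers outcome is descriptive. Only smoking, exercise and salt are followed up at six months for a between-arm test. A reader might also infer that rewording the analysis section is enough. That would hold if villages were randomised, but the protocol randomises two nine-village areas, and the illustration above shows that a village model leaves part of the error in place.

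**Conclusion.** The point holds and should be fixed before analysis. The stated methods give standard errors, confidence intervals and p-values that are too small for SBP, DBP and the between-arm smoking, exercise and salt outcomes whenever the ICC is positive.

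With an assumed ICC of 0.01 to 0.05, a nominal 5% test has actual size of about 6%-14% from village clustering alone (11.8 to 16.7 per village). For the allocation as written, with 106 per arm, the size is about 17%-43% at nominal 5% and about 7%-30% at nominal 1%. These figures rest on the assumed ICC, equal unit sizes and a normal approximation; the direction does not depend on the ICC chosen. With one cluster per arm, area is confounded with treatment, and no analysis of the data can recover the missing between-area variance.

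**What to change.** Replace the independence-based models in Statistical analyses, and align the Abstract:

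- For SBP and DBP, use a baseline-adjusted linear mixed model with a random village intercept and small-sample degrees of freedom (Kenward-Roger or Satterthwaite), or compare 18 baseline-adjusted village means on t with about 16 df.
- For smoking, exercise and salt, use GEE by village with a small-sample variance correction, or compare village-level proportions.

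Then settle the unit of randomisation, by one of two routes:

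- Randomise the 18 villages individually, which makes these analyses fully valid. This changes Cluster randomization and Sequence generation. Randomisation is planned after recruitment and baseline data collection, so recruitment need not change.
- If the two-area allocation stands, or has already been carried out, still use the village-level analysis. State in the plan and the report that inference assumes no variation between the two areas apart from the intervention.

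The cost is wider confidence intervals and less power than Sample size states. With 106 per arm at two-sided 0.01, the 67.6% found above falls to about 62% at village ICC 0.01 and about 45% at 0.05 (effective numbers 106/1.11 = 96 and 106/1.54 = 69 per arm). The sample-size statement should be revisited with a stated ICC.

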**Methods:**

A single-center cluster randomized controlled trial (RCT). The study will be conducted for 6 months, a total of 300 participants of age 30 to 75 years with 150 adults in each of the intervention and the control arms. The intervention arm will involve the delivery of a blended learning education program on lifestyle changes for the management of high blood pressure. The education program comprises evidence-based information with pictures, fact sheets, and published literature about the effects of high blood pressure on CVD development, increased physical activity, and the role of a healthy diet in blood pressure management. The control group involves providing information booklets and general advice at the baseline data collection point. The primary outcome will be the absolute difference in clinic SBP and DBP. Secondary outcomes include the difference in the percentage of people adopting regular exercise habits, cessation of smoking and reducing sodium chloride intake, health literacy of all participants, and the perceived barriers and enablers to adopt behavior changes by collecting qualitative data. Analyses will include analysis of covariance to report the mean difference in blood pressure between the control and the intervention group and the difference in change in blood pressure due to the intervention.

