### Outcome measures

#### Primary outcome

The primary outcome is the difference in clinical SBP and DBP within and between control and intervention groups. We will report both the absolute difference and the difference in change after follow-up.

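### Baseline blood pressure enters the primary model only if the arms happen to differ on it, which gives up precision and leaves the analysis unreconciled with the ANCOVA named in the abstract

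*Protocol article*

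**What the plan says.** The Statistical analyses section of the protocol article takes three steps.

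- It compares the arms at baseline by significance tests: "The baseline characteristics for the intervention and the control group will be examined using the chi-square test or Fisher’s exact test for categorical variables", with a t-test or Mann-Whitney test for continuous variables. It expects that differences may occur because clusters are randomised.
- It defines the effect as a difference in change: "it could be shown as the difference between DifCon and DifInt", where "DifCon equals the difference between baseline and follow-up for the control group" and DifInt is the same quantity for the intervention arm. It adds that this comparison yields the true effect of the intervention.
- It names the model, "Generalized linear model (GLM) will be used for analytical purpose", and the covariate rule, "the models will be adjusted for factors which are different between control and intervention groups at baseline". No covariate is guaranteed, and baseline SBP and DBP are not named.

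The abstract (Methods) says: "Analyses will include analysis of covariance to report the mean difference in blood pressure between the control and the intervention group". That sentence goes on to include the difference in change as well. The Primary outcome section says: "We will report both the absolute difference and the difference in change after follow-up". ANCOVA is in the abbreviation list, but the Methods text never uses it.

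**The concern.** Baseline blood pressure is the obvious prognostic covariate for blood pressure at 6 months, and it is measured on everyone before randomisation. Under the stated rule it enters the model only if it is found to differ between arms. A baseline test measures how far the arms differ by chance. It does not measure how strongly a variable predicts the outcome, which is what decides whether adjustment gains precision. The rule also makes the primary model depend on the data.

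Two things are at stake. Precision that costs nothing is given up. And where a chance imbalance is too small to be flagged, regression to the mean moves the change-score contrast in favour of the arm that starts higher. In addition, if nothing differs at baseline, the Methods model is a plain comparison of changes and not the analysis of covariance that the abstract announces.

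**Working it through.** **Inputs from the protocol.** Sample size section: 106 evaluable per group, difference 5 mmHg, SD 12 mmHg, alpha 0.01, 95% power. Cluster randomization section: 150 per arm at baseline.

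**Assumptions.** Alpha is two-sided (not stated). SD 12 is the SD of SBP at one time point (not stated). The correlation r between baseline and follow-up SBP is not in the document; the range tried is 0.3 to 0.8. A baseline difference is judged at p < 0.05 (no threshold is given). Clustering is ignored throughout.

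**The plan's own figure.** n per group = 2(2.576 + 1.645)² × 12²/5² = 205.2, so 206, against 106 stated. With 106 per group, SE = 12 × √(2/106) = 1.648, 5/1.648 − 2.576 = 0.458, and power is 67.6%. The stated 95% is therefore not reproduced. That is a separate matter; 106 per arm is kept below as the protocol's design.

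**Precision.** SD of change = 12√(2(1−r)). Residual SD with baseline in the model = 12√(1−r²). The variance ratio is 2(1−r)/(1−r²) = 2/(1+r).

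| r | Variance ratio | Power, change score | Power, baseline included | n per arm for 95% power (change score / baseline included) |
|---|---|---|---|---|
| 0.3 | 1.54 | 49.5% | 72.7% | 288 / 187 |
| 0.5 | 1.33 | 67.6% | 82.3% | 206 / 154 |
| 0.7 | 1.18 | 91.0% | 95.3% | 124 / 105 |
| 0.8 | 1.11 | 98.7% | 99.3% | 83 / 74 |

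If SD 12 is instead the SD of change, the change score has 67.6% power at every r, and including baseline gives 88.2%, 82.3%, 76.2% and 73.3% at r = 0.3, 0.5, 0.7 and 0.8. The direction is the same.

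**The rule itself.** It was simulated with 20,000 trials per setting and 106 independent participants per arm: a change score, with baseline SBP added only when its t-test gave p < 0.05. Baseline SBP entered in about 5% of trials. Power was 49.6%, 67.5% and 90.9% at r = 0.3, 0.5 and 0.7. The unadjusted change score gave 48.4%, 66.4% and 90.4%, and baseline always included gave 71.9%, 81.1% and 95.0%. The rule thus recovers only 0.5 to 1.2 percentage points. Its type I error at alpha 0.01 was 0.006 to 0.009, and the mean estimate was unbiased.

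**Imbalance that escapes the rule.** With 150 per arm, a difference of up to 1.96 × 12 × √(2/150) = 2.7 mmHg stays non-significant. The unadjusted change score is then off by (1−r) times the imbalance:

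- r = 0.3: 0.7 × 2.7 = 1.9 mmHg, 38% of the 5 mmHg target
- r = 0.5: 0.5 × 2.7 = 1.4 mmHg, 27%
- r = 0.7: 0.3 × 2.7 = 0.8 mmHg, 16%

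**The case against.** Several points on the other side have force.

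- *The protocol never says that selection is by p-value, or that only differing factors may enter.* This is right as to the wording. The reading rests on two nearby statements, the baseline tests and the adjustment rule. On any reading, though, baseline blood pressure is not guaranteed a place.
- *A Gaussian GLM with covariates can be an ANCOVA, and the abstract and Primary outcome section share the same two contrasts.* This stands. A reader might infer that abstract and Methods contradict each other outright. The document does not support that: the abstract names no covariate. The two passages are unreconciled, because the Methods model becomes an ANCOVA only if some covariate happens to be selected.
- *The bias is not systematic.* This stands. A reader might infer that the change score is biased or produces false positives. Averaged over randomisations the bias is about zero, and type I error was below nominal in the simulation. The shift is conditional on the imbalance that occurs. A larger imbalance, such as 3 mmHg, would give z = 3/1.386 = 2.17 with 150 per arm and would be flagged, so the rule would adjust for it.
- *If the imbalance is a stable difference between the two nine-village areas, each arm regresses to its own mean; the change score is then free of this bias and ANCOVA may carry it.* This also stands. The (1−r) formula is for chance imbalance around a common mean. With one cluster per arm the data cannot tell the two cases apart.
- *Covariate lists are usually left to the analysis plan.* This is true of a missing list, but the article does not leave the matter open: it states a selection rule.

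**Conclusion.** The point holds as one of precision and clarity. The Statistical analyses section fixes a covariate rule that does not secure baseline SBP or DBP in the primary model, and the abstract and Methods do not describe the same model. The loss is certain in direction. Its size depends on r: 23 percentage points of power at r = 0.3, 15 at r = 0.5, 4 at r = 0.7 and under 1 at r = 0.8, under the protocol's 106 per arm, alpha 0.01 two-sided, and SD 12 read as the SD of SBP. The possible shift of 0.8 to 1.9 mmHg is a conditional one, for a chance imbalance just below an assumed 0.05 threshold. All figures treat participants as independent, so they compare the two analyses and do not give the trial's real power. This should be changed, but it does not by itself invalidate the trial.

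**What to change.** - Delete the selection of covariates by baseline difference.
- State the primary model as follow-up SBP on arm with baseline SBP always included, and likewise for DBP. Add a short prespecified list of variables already recorded or assessed at baseline, for example age, sex and antihypertensive use.
- Use this model in the abstract, the Primary outcome section and the Statistical analyses section. With baseline in the model, the arm coefficient is the same whether the response is follow-up or change, so the two between-arm contrasts in the Primary outcome section become one estimate.

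The cost is analysis wording only; blood pressure is already measured before randomisation. The change does not touch the separate problem that one coin toss allocates two clusters: no covariate can separate the effect of the arm from that of its single cluster.
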